# Study patients

Late-stage elderly patients (75 years or older) with NVAF
(Regardless of whether anticoagulants are administered or not, and whether anticoagulants are used.)

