| Clinically relevant bleeding (Clinically relevant non-major bleeding) | Clinically evident bleeding requiring treatment. Examples include, but are not limited to, diagnostic tests and treatments listed below. Outpatient visits without any of the following or similar medical procedures (diagnostic tests and treatments) do not fall under "require treatment."  ・ Inpatient hospitalization or prolongation of existing hospitalization  ・ Laboratory tests  ・ Imaging test  ・ Endoscopy; colonoscopy; cystoscopy; bronchoscopy  ・ Nasal packing  ・ Compression tourniquet  ・ Ultrasound-guided aneurysm closure  ・ Coil embolization  ・ Inotropic support  ・ Surgery  ・ discontinue or discontinuation of anticoagulant therapy as directed by the physician  ・ Change of concomitant treatment other than anticoagulants (reduction or discontinue of aspirin, etc.) as directed by the physician |
| Minor bleeding [Minor (not clinically relevant) bleeding] | Other obvious bleeding that does not meet the criteria for major bleeding or clinically important bleeding (e.g., epistaxis without treatment). |

1 Modified definitions of phase III, MNCT ^2525^

1. Other events

Presence or absence of falls and fractures (extrinsic or intrinsic)

If yes,

Name of the adverse event, date of onset, PT-INR immediately before the event, presence or absence of antiplatelet therapy immediately before the event, type, seriousness, procedure, other procedure, outcome, date of outcome, drug(s) related to the event, drug(s) possibly related to the event, comments about the adverse event(s)

1. Other adverse events

If a serious adverse event occurs or if Licciana is administered within one week before the onset of the adverse event, the following items will be investigated.

Name of adverse event, date of onset, seriousness, procedure, other procedure, outcome, date of outcome, drug(s) of causal relationship, drug(s) other possible cause(s), adverse event(s)

(10) For (14), the study subject will be contacted by telephone or letter even if there is no visit, and the event status will be checked at 12 and 24 months.

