## Sub-cohort study A: assessment markers

To compare the association of coagulation and fibrinolytic molecular markers, antithrombotic activity with stroke/systemic embolism, and hemorrhagic adverse events by non-anticoagulant, warfarin, and DOAC.

Endpoint

1. Prothrombin time (PT), PT-INR, activated partial thromboplastin time (APTT), TTR, D-dimer, soluble fibrin monomer complex (SFMC), prothrombin fragment 1+2 (F1+2), thrombin-antithrombin complex (TAT), sensitive troponin I, brain natriuretic polypeptide (BNP) precursor N-terminal fragment (NT-pro BNP).
2. Stroke/systemic embolism
3. Hemorrhagic adverse events

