## Analysis of follow-up data

Frequencies and event rates and their 95% confidence intervals will be calculated for the following items:Cox proportional hazards models and logistic regression analysis are used to search for risk factors.

1. Type, dose, number of daily doses, and frequency of changes of anticoagulants and antiplatelet agents [at 12 and 24 months of follow-up]
2. Incidence of stroke/systemic embolism at 24-month follow-up

- Stroke (atherosclerotic, cardiogenic, lacunar, haemorrhagic, unclassifiable, other stroke, TIA)
- Systemic embolism

1. Incidence rate of bleeding adverse events [at 24-month investigation] (see Table 4 for classification of bleeding and definitions)Table 44

- Major bleeding
- Clinically relevant bleeding
- Minor bleeding
- Intracranial hemorrhage
- Gastrointestinal bleeding (upper and lower)

1. Number of falls
2. Incidence of bone fractures
3. Mortality (all deaths, cardiovascular deaths, non-cardiovascular deaths)
4. Incidence of myocardial infarction, cardiac intervention, and heart failure requiring hospitalization

(1) For ~(7), the CHADS score, the CHA _2_ DS_2_-VASc score, the HAS-BLED score and its constituent factors, the factors identified as risk factors in the guideline, the factors identified as risk factors in the present study, the presence or absence of anticoagulant therapy and type (DOAC, warfarin), dosage, PT-INR, etc. will be examined by subgroup.

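### Table 4 lets stopping the anticoagulant alone make a bleed clinically relevant, which tilts the section 17.3 comparison of that one class by presence or absence of anticoagulant

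*Protocol*

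**What the plan says.** The bleeding classes are set in Table 4, in section 11.3 (12-month and 24-month surveys). The middle class is defined as: "Clinically evident bleeding requiring treatment. Examples include, but are not limited to, diagnostic tests and treatments listed below". The table then narrows what counts as treatment: "Outpatient visits without any of the following or similar medical procedures (diagnostic tests and treatments) do not fall under" that term. Among the listed items is "discontinue or discontinuation of anticoagulant therapy as directed by the physician". The next item is its counterpart for other drugs: "Change of concomitant treatment other than anticoagulants (reduction or discontinue of aspirin, etc.) as directed by the physician". Whatever is left over is minor: "Other obvious bleeding that does not meet the criteria for major bleeding or clinically important bleeding".

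Section 4 (Study patients) admits patients without an anticoagulant: "Regardless of whether anticoagulants are administered or not, and whether anticoagulants are used".

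Section 17.3 lists clinically relevant bleeding as a separate line among the bleeding outcomes. For all its follow-up items it states that "the presence or absence of anticoagulant therapy and type (DOAC, warfarin), dosage, PT-INR, etc. will be examined by subgroup".

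**The concern.** An outcome class should mean the same thing in the groups it is used to compare. Here one route into the class is open only to patients who are taking an anticoagulant when they bleed. Take two patients with the same nosebleed and no test, local treatment or change of another drug. The one whose physician stops the anticoagulant counts as clinically relevant. The one who takes no anticoagulant counts as minor.

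The exposure thus helps to define the outcome. Adjusting for patient characteristics does not remove this, because the difference arises in the classification of the bleed and not in the patients' risk. What is at stake is the reading of one line of section 17.3, in a study that aims to describe who should receive a DOAC.

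**Working it through.** **Step 1: is one item enough?** Table 4 withholds the class only from visits with none of the listed or similar actions. A single item therefore qualifies, and stopping the anticoagulant is one of them.

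**Step 2: who can meet the item?** Only a patient on an anticoagulant at the time of the bleed. The other listed items (hospitalization, laboratory tests, imaging, endoscopy, nasal packing, compression, surgery, change of another drug such as aspirin) are not tied to anticoagulant use.

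**Step 3: where is the class compared by exposure?** In section 17.3, by presence or absence of anticoagulant therapy.

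**Step 4: how large could the shift be?** The protocol gives no figure to reproduce and no input for this, so the following is an illustration. Suppose true bleeding is identical in treated and untreated patients. Among non-major evident bleeds let

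- c = share meeting at least one item open to everyone (assumed 0.3 to 0.9);
- q = share of the remainder in which a treated patient has only the anticoagulant stopped (assumed 0.05 to 0.4).

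Untreated patients have a share c classed as clinically relevant and 1 - c as minor. Treated patients have c + q(1 - c) and (1 - q)(1 - c). The spurious ratios, treated to untreated, are

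- clinically relevant: (c + q(1 - c)) / c;
- minor: (1 - q)(1 - c) / (1 - c) = 1 - q.

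For example, c = 0.3 and q = 0.4 give (0.3 + 0.28) / 0.3 = 1.93. At the other end, c = 0.9 and q = 0.05 give (0.9 + 0.005) / 0.9 = 1.01.

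| c | ratio at q = 0.05 | q = 0.1 | q = 0.2 | q = 0.4 |
|---|---|---|---|---|
| 0.3 | 1.12 | 1.23 | 1.47 | 1.93 |
| 0.5 | 1.05 | 1.10 | 1.20 | 1.40 |
| 0.7 | 1.02 | 1.04 | 1.09 | 1.17 |
| 0.9 | 1.01 | 1.01 | 1.02 | 1.04 |
| Minor bleeding, any c | 0.95 | 0.90 | 0.80 | 0.60 |

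**Step 5: what stays unaffected?** Events only move between two adjacent classes, so all bleeding combined keeps a ratio of 1.00. Major bleeding is defined by fatality, critical site, or haemoglobin fall with transfusion, none of which refers to stopping a drug. Intracranial and gastrointestinal bleeding are reported by site. All of these stay at 1.00.

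**Step 6: does the remedy work?** If bleeds that qualify only through stopping the anticoagulant are left out, the treated share returns to c and the ratio is c / c = 1.00.

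**The case against.** The strongest reply is that a bleed serious enough for a physician to stop the anticoagulant is clinically relevant, and that the list is so broad that few bleeds depend on this item alone. The first part is fair for description, and it is why Table 4 should stay for the overall tabulation. It does not justify a comparison with patients to whom the item cannot apply. The second part stands as a limit on size: a laboratory test alone qualifies, and at c = 0.9 the ratio is only 1.01 to 1.04.

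It can also be said that the remedy belongs in the separate SAP, which is not at hand, and that section 11.3 already collects the action taken for each bleed, with section 10.2.1 listing what was done with the anticoagulant and any other treatment. That is partly right. However, the protocol itself fixes the class definition, and section 11.3 records the class without the Table 4 item that qualified it. Diagnostic tests, which also qualify, may not be fully captured in the action fields. An SAP could then not reliably isolate the bleeds concerned.

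A reader might infer more than the protocol supports:

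- **That bleeding in general is biased against treatment.** It is not. The bleeding-related secondary endpoints in section 15 are major bleeding, hemorrhagic stroke and intracranial hemorrhage, and clinically relevant bleeding is not an endpoint there.
- **That untreated patients can never reach the class.** They can, by every other item. A patient untreated at baseline who starts an anticoagulant later can meet this one too.
- **That sub-cohort study A is affected in the same way.** Section 16.1 does mention "hemorrhagic adverse events by non-anticoagulant, warfarin, and DOAC", but its aim is the association of markers with events. The analyses in section 17.5.1 are by TTR, PT, APTT and marker level, and none contrasts bleeding in treated and untreated patients.
- **That bleeding will seem to fall once treatment stops.** No analysis across stopping is planned.

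**Conclusion.** The point holds for one comparison. Clinically relevant bleeding by presence or absence of anticoagulant, as planned in section 17.3, is shifted against treatment, and minor bleeding is shifted in the opposite direction. The direction follows from the definition as soon as any treated patient qualifies only by stopping the anticoagulant.

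The size cannot be known from the protocol: about 1.01 to 1.93 for clinically relevant bleeding and 0.95 to 0.60 for minor bleeding, resting wholly on the assumed c and q and on equal true bleeding. It may well lie near the low end. DOAC-versus-warfarin comparisons are not affected through absence of treatment, since both groups can meet the item. This is worth correcting because the remedy is cheap, but it does not touch the primary endpoint or the major-bleeding endpoint.

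**What to change.** Keep Table 4 unchanged for the overall tabulation. On the bleeding form, record which listed item or items qualified the bleed. In section 17.3, for comparisons by presence or absence of anticoagulant, report clinically relevant bleeding without events that qualify only through stopping the anticoagulant, beside the result under the full definition. Rest the treated-versus-untreated conclusion on major bleeding.

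The cost is one form field and one derived variable, with slightly fewer events and so slightly wider intervals in that comparison. No clinical rule changes, and section 17.5.1 needs no change on this account.

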# Schedule of research

Table 55 Observation and examination schedule

The investigation items are as follows and will be conducted within the scope of daily medical care.

| Time of investigation  Survey item | Eligibility Confirm | Baseline Study  (-180-0 days) | 12 months Study  (±60 days) | 24 months Study  (±60 days) |
| --- | --- | --- | --- | --- |
| Confirmation of consent, inclusion and exclusion criteria | ○ |  |  |  |
| Withdrawal of Informed Consent, Visit Status, and Confirmation of Health |  |  | ○ | ○ |
| Patient characteristics, history of previous treatment for AF, surgical history, history of bleeding, past medical history (other than bleeding), complications, etc. |  | ○ |  |  |
| Status of anticoagulation administration |  | ○ | ○ | ○ |
| Status of administration and compliance with drugs other than anticoagulants |  | ○ | ○ | ○ |
| Status of non-pharmacologic therapy for AF |  | ○ | ○ | ○ |
| Implementation status of invasive procedures (including minor surgical ^1^) other than AF treatment |  |  | ○ | ○ |
| Clotting studies (PT-INR) |  | ○ | ○ | ○ |
| Clinical course and laboratory values |  | ○ | ○ | ○ |
| Presence or absence of cardiovascular events, gastrointestinal bleeding, bleeding adverse events, falls, fractures, deaths, or other adverse events |  |  | ○ | ○ |
| Sub-cohort study |  |  |  |  |
| A. Assessment marker |  | ○  (central measurement) |  |  |
| B. Echocardiogram |  | ○ | ○ | ○ |
| C. Heart rate |  | ○ | ○ | ○ |
| D. Hypertension |  | ○ |  |  |
| E. Cognitive functioning |  | ○ |  | ○ |
| F. Frail |  | ○ |  |  |
| G. Adherence |  | ○ |  | ○ |

AF, atrial fibrillation; PT-INR, prothrombin-international normalized ratio

1 Minor surgery includes procedures involving biopsy and puncture

# Number of target registrations of study subjects

30,000 patients (consecutive enrollment) in the study as a whole

Rationale for target enrollment

The incidence of stroke/systemic embolism in Fushimi AF Registry's ^5^ has been reported to be 5.1/100 patients aged 85 years or older, 2.0/100 patients aged 84 years or younger, and a hazard ratio of 1.77 for patients aged 85 years or older to patients aged 75 years or older and 84 years or younger.

Based on this assumption, the incidence rates in patients aged 75 to 84 years and those aged 85 years and older are 2.9 per 100 person-years and 5.1 per 100 person-years, respectively, and the overall incidence rate is estimated to be about 3.5 per 100 person-years, assuming a patient composition ratio of 3:1 in this study.

We estimate the incidence of stroke/systemic embolism in patients without risk factors for this study to be 3.4/100 person-years. Assuming an exponential distribution (constant hazard) in time to onset, if the proportion of patients with risk factors is 5%, enrolling 30,000 patients will detect a hazard ratio of 1.3 for the development of stroke/systemic embolism with risk factors to no risk factors over a 2-year follow-up period of at least 5% with a two-sided significance level of at least 80% power.

For 30,000 patients, the power of 80% is to detect risk factors with a hazard ratio of about 1.5, even for intracranial hemorrhage, which is a low incidence but of particular concern, among the events planned to be studied. An estimated incidence of 1.2% per year of intracranial bleeding and a risk factor of 5% were assumed [e.g., a potential intracranial bleeding risk of 1.5 times greater than that of patients without SRI in patients with severe renal dysfunction (SRI)] would detect a statistically significant risk increase of 80% even with an SRI of about 5% of patients overall.

# Study Period

Date of approval by the ethics review committee of the responsible medical institution-September 2020

(Registration period: Date of approval by the ethics review committee of the research institution-September 2018, follow-up period of 2 years)

However, the registration period may be shortened and the planned implementation period may be shortened or extended by the agreement of the Central Committee for Research, the principal investigator and the sponsor.

# Endpoint

## Primary endpoint

Incidence of Stroke/Systemic Embolism during the Observation Period

## Secondary endpoint

Occurrence of the following events during the observation period

1. Hemorrhagic Adverse Events (Major Bleeding)
2. Stroke
3. Systemic embolism
4. Ischemic stroke
5. Hemorrhagic stroke
6. Intracranial hemorrhage
7. Cardiovascular events (stroke, myocardial infarction, non-myocardial infarction cardiac intervention, heart failure requiring hospitalization)
8. Death due to cardiovascular disease (death due to cardiovascular causes undeniable)
9. All deaths

## Other evaluation items

Incidence of falls and fractures

# Implementation of Sub-Cohort Study (Sub-Study 1)

Along with the conduct of this study, we conduct the following subcohort studies:As far as possible, investigators at participating medical institutions that have declared their cooperation in each sub-cohort study at the time of their participation in this clinical study will conduct a survey of all research subjects registered in the relevant study institution, which is set out for each of the following sub-cohort studies.

Each subcohort study will be conducted at the time of the survey in Table 1 Observations and Tests Schedule, and the details will be in accordance with the separately developed Sub-Cohort Study Protocol (Appendix).Table 11Observation and examination schedule

Acceptable

Baseline (most recent information within 180 days of the date of obtaining informed consent, unless otherwise specified)
12-month and 24-month surveys: both ±60 days

## Sub-cohort study A: assessment markers

To compare the association of coagulation and fibrinolytic molecular markers, antithrombotic activity with stroke/systemic embolism, and hemorrhagic adverse events by non-anticoagulant, warfarin, and DOAC.

Endpoint

1. Prothrombin time (PT), PT-INR, activated partial thromboplastin time (APTT), TTR, D-dimer, soluble fibrin monomer complex (SFMC), prothrombin fragment 1+2 (F1+2), thrombin-antithrombin complex (TAT), sensitive troponin I, brain natriuretic polypeptide (BNP) precursor N-terminal fragment (NT-pro BNP).
2. Stroke/systemic embolism
3. Hemorrhagic adverse events

## Subcohort study B: Echocardiogram

To investigate underlying heart disease by echocardiography, left ventricular (LV) and left atrial (LA) structure and function, and their association with stroke/systemic embolism.

Endpoint

1. Structure and function of LV:

- Left ventricular end-diastolic dimension (LVDd)/left ventricular end-systolic dimension (LVDs)/interventricular septal wall thickness (IVSTD)/left ventricular posterior wall thickness (PWTD)
- Left ventricular end-diastolic volume (LVEDV)/left ventricular end-systolic volume (LVESV)/left ventricular ejection fraction (LVEF)
- Stroke volume (SV)
- LV mass index (LV mass index)
- LV sphericity index (1) Left ventricular end-diastolic volume (LVEDV) /π*LV length: ^3^ /6, 2) LVDd/LV length)
- LV wall abnormal motion

1. LA structure and function:

- Left atrial diameter (LAD)
- LA expansion index by left atrial volume* (LA volume) (peak LA volume [LA _max_], minimum LA volume [LA _min_] and atrial pre-contraction LA volume [LA _pre-A_ ]), calculated values of total/passive/active LA emptying fraction

1. Structure and function of the right ventricle (RV):

- Tricuspid systolic pressure gradient (TRPG), inferior vena cava diameter (IVCD), estimated right atrial pressure (RAP) from respiratory variability, and estimated pulmonary artery systolic pressure (PASP)
- RV function [Tricuspid Annular Systolic Migration Distance (TAPSE) and Tricuspid Annular Systolic Velocity (TVS)].

1. Doppler imaging

- LV inflow early diastolic wave (E), LV inflow atrial systolic wave (A), mitral annular early diastolic velocity (TDI e'), and mitral annular atrial systolic velocity (TDI a').

1. Valvular heart lesions (mitral, aortic, tricuspid, pulmonic, prosthetic, and valve repair)
2. Stroke/systemic embolism

## Sub-Cohort Study C: Heart Rate

To evaluate the association between heart rate during the development of AF recorded on an electrocardiogram and the risk of developing stroke/systemic embolism.

Endpoint

1. Heart rate
2. Stroke/systemic embolism

## Sub-cohort study D: Hypertension

To investigate the relationship between blood pressure (office and home blood pressure) and stroke/systemic embolism and bleeding adverse events.

Endpoint

1. Office blood pressure and home blood pressure
2. Stroke/systemic embolism
3. Hemorrhagic adverse events

## Sub-cohort study E: cognitive function

To clarify the actual status of cognitive function and to investigate the factors affecting cognitive function in late-stage elderly patients with NVAF. Information on cognitive function and social activity will be collected using the Mini-Mental State Examination (Mini Mental State Examination,MMSE), which measures cognitive function (see Sub-Cohort Study E Protocol, Appendix 1) and the Social Activity Questionnaire (see Sub-Cohort Study E Protocol, Appendix 2).

Endpoint

1. Mini-Mental State Examination(MMSE) scores.
2. Social activity level

## Sub-cohort study F: Frail

To ascertain the percentage of frail patients in late-stage elderly patients with NVAF and to check the status and status of use of anticoagulation therapy in frail patients. We will also explore the relationship between frail and stroke/systemic embolism and bleeding adverse events. Information on the frail will be collected using questionnaires related to the frail [Abbreviated Flail Scale (National Center for Longevity Medical Research) (Sub-Cohort Study F Implementation plan, Appendix 1), Basic Checklist for the Elderly (Ministry of Health, Labour and Welfare) (see Sub-Cohort Study F Protocol, Appendix 2), and questionnaires on living conditions (presence and grade of certification of need for nursing care, presence or absence of a cohabiting person, composition of a cohabiting family)].

Endpoint

1. Frailty score
2. Basic checklist evaluation value for the elderly
3. Questionnaires on living conditions
4. Stroke/systemic embolism
5. Hemorrhagic adverse events

## Sub-cohort study G: adherence

To investigate the comprehensibility of medication adherence and NVAF in older patients with NVAF, and to investigate the association between medication adherence and NVAF comprehension, stroke/systemic embolism, and hemorrhagic adverse events. Adherence information will be collected by the Adherence Questionnaire [Morisky Medication Adherence Scale(MMAS] ^26^ Score and NVAF Comprehensibility Questionnaire. There are two types of MMAS: a MMAS-4 consisting of four-item questions and a MMAS-8 consisting of eight-item questions (Sub-Cohort Study G Protocol, see Appendix 1). This subcohort research employs a MMAS-8 that provides a more accurate picture of patients' medication adherence. We will also investigate the percentage of days prescribed (Proportion of days covered, PDCs) to the time of enrollment.^26^

Endpoint

1. MMAS-8 Score
2. NVAF comprehensibility
3. Percentage of days prescribed (Proportion of days covered, PDCs)
4. Stroke/systemic embolism
5. Hemorrhagic adverse events

# Statistical Analysis

Statistical analysis will be performed by tabulating survey information based on the following provisions. Detailed analysis methods and items not described below will be subject to a separate Statistical Analysis Plan.

